### Termination and withdrawal criteria

2.9

All participants will be informed that they have the right to withdraw from the trial and if they do, they will also receive the standard treatment. The reason for withdrawal will be recorded in their case report file (CRF). The criteria for discontinuing treatment and withdrawing patients from the study are:

(1)The experience of adverse events related to taking the drugs, and the researchers determine that it is not appropriate to continue administering the drugs(2)Required treatment for another serious disease during the study(3)Poor compliance or withdrawal midway through the study(4)Inability to tolerate 2 weeks of the intervention and cannot continue the research due to the automatic requirement of discharge or transfer(5)Giving up treatment in advance due to economic burden and/or other factors(6)The experience of a serious adverse event in the process of the trial, such as a life-threatening incident or even death, and the researchers could not continue

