### Determination of results

3.2

Since a holistic view of the patient is the core value of TCM, there is no single index that can predict their rehabilitation in order to evaluate the efficacy of JWQYD. Therefore, ARDS needs to be comprehensively evaluated.

1. Efficacy rate: The efficacy rate will be calculated according to the TCM syndrome score (Table 3).^[23]^ The total efficacy rate (%) = (clinical control + significant effect + effective)cases/(total cases × 100%). The score reduction (%) = (points before treatment - points after treatment)/(points before treatment × 100%). The TCM syndrome score will refer to the standard for the diagnosis and curative effect of TCM syndrome issued by the Chinese Society of TCM in 2012.

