### Compliance

3.4

Once the patients are randomly divided into groups, the researchers will pay close attention to the patients’ vital signs. In the case of any drug-related adverse events or other disease conditions, the physical condition of the patients will be evaluated immediately to determine whether they can continue to participate in the study and effective interventions will take place for any adverse events.

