### Adverse events

3.5

Regardless of its relationship with the study intervention, any adverse event will be recorded in the CRF. If any serious adverse event occurs, the intervention will be stopped immediately and details concerning the time, severity, relationship to the drug, and corresponding measures will be taken according to the standard operating procedures of the Chinese Food and Drug Administration. In addition, serious adverse events will be reported to the steering committee and ethics committee within 24 hours.

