### Statistical analyses

3.7

Before analysis, 2 similar participants with complete data will be carefully examined to ensure that the data is correct. All data analyses will then be based on treatment intention.

The data will be analyzed using the statistical software package SPSS 22.0 (Chicago, IL). The analysis method will be selected according to the distribution characteristics of the data. The measured data will be expressed as the mean ± the standard deviation. First, the normal test and the homogeneity test of variance will be performed. In the case of normal distribution and equal variance, a *t*-test will be performed; otherwise, a nonparametric test will be utilized. The difference will be statistically significant when *P* ≤ .05.

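### Section 2.9 uses one list for stopping the drug and for leaving the study, so outcomes that the intention-to-treat analysis needs may go uncollected

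*Protocol article*

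**What the plan says.** Section 2.9 (Termination and withdrawal criteria) introduces its list with "The criteria for discontinuing treatment and withdrawing patients from the study are". No item is assigned to only one of the two actions. Item 1 is a dosing decision: after a drug-related adverse event, "the researchers determine that it is not appropriate to continue administering the drugs". Item 2 is the need to treat another serious disease. Item 3 reads "Poor compliance or withdrawal midway through the study". Item 4 is failure to tolerate the two-week course together with inability to go on in the research because of discharge or transfer. Item 5 is giving up treatment early, for cost or other reasons. Item 6 is a serious adverse event, "such as a life-threatening incident or even death, and the researchers could not continue". For patients who withdraw, the section provides standard treatment and a recorded reason.

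Section 3.4 (Compliance) says that after a drug-related adverse event or another disease condition the patient is evaluated "to determine whether they can continue to participate in the study".

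Section 3.7 (Statistical analyses) says: "All data analyses will then be based on treatment intention". The efficacy rate in section 3.2, on which section 2.4 bases the sample size, is built from "points before treatment - points after treatment". Section 3.2 also lists 28-day mortality, and deaths and readmissions over the year after discharge. Section 3.8 plans follow-up by telephone.

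**The concern.** Stopping the study drug and leaving the study are different events. Under intention to treat, a patient who stops the drug still counts in the assigned arm, and the outcome is still wanted. A site that applies section 2.9 literally has grounds to withdraw such a patient, and may then stop collecting data.

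The efficacy rate is most exposed. Without a post-treatment score, a patient cannot be placed in any of the four effect classes in section 3.2. For a survivor withdrawn early, 28-day and 1-year status may also go uncollected. Patients who stop because of an adverse event, another serious disease or poor compliance are unlikely to be a random subset. If such withdrawals differ between arms, the comparison can be biased even when blinding holds.

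An analysis plan cannot repair this afterwards. It can choose how to handle a missing value, but it cannot recover a score or a vital status that was never recorded.

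**Working it through.** **Reading the six items of section 2.9**

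| Item | Treatment or illness reason | Wording on leaving or being unable to continue |
|---|---|---|
| 1 Drug-related adverse event | yes | none |
| 2 Another serious disease | yes | none |
| 3 Poor compliance / withdrawal midway | yes (first half) | yes (second half) |
| 4 Intolerance, with discharge or transfer | yes | yes |
| 5 Giving up treatment | yes | none |
| 6 Serious adverse event | yes | yes |

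Items 1, 2 and 5 and the first half of item 3 are thus treatment or illness events that the heading also makes grounds for leaving the study. Items 4 and 6 and the second half of item 3 carry study-level wording of their own.

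**Setting the sections side by side**

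1. Section 2.9, item 1: the trigger is that dosing should not continue, and the heading attaches both consequences to it.
2. Section 3.4: for the same trigger, the question is participation in the study.
3. Section 3.7: all analyses follow intention to treat, so outcomes are needed whatever happened to dosing.
4. Section 3.2, item 1: the efficacy rate needs a score after treatment. I take this as the end of the two-week course in section 2.1; the schedule figure is not shown.
5. No section shown says that patients who stop the drug remain in follow-up.

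Steps 1 and 2 permit the removal of patients whom step 3 needs.

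**The plan's own sample size, for context**

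Inputs from section 2.4: effective rates 65.2% and 34.8%, loss 10%, total 110. Power and sidedness are not stated; I assume 80% and two-sided 5%, with a continuity-corrected comparison of two proportions. This gives 48 per arm. Inflated for loss: 48 / (1 − 0.10) = 53.3, rounded up to 54 per arm, or 108 in total, within 2 of the stated 110. The finding does not depend on this figure.

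**Scale of one lost outcome**

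- Patients per arm at 1:1 (section 2.1): 110 / 2 = 55.
- One unknown outcome: 1 / 55 = 1.8 percentage points of an arm's efficacy or 28-day mortality rate.
- If k outcomes in an arm are unknown, that arm's rate among all randomised is uncertain by k / 55. Taking k = 1, 5 and 11 purely as assumptions gives 1.8, 9.1 and 20.0 points.
- The planned difference is 65.2 − 34.8 = 30.4 points.

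These are bounds under assumed counts, not estimates. The documents give no rate of drug stops or withdrawals.

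**The case against.** The best reply is that the harm is inferred. Section 2.9 nowhere says that outcome collection ends, and a condensed article may leave follow-up after a drug stop to the full protocol. Other text points towards keeping patients: intention to treat in 3.7, 28-day mortality counted from the start of the trial, one year of follow-up for both groups in 2.1, telephone contact in 3.8, and a 10% allowance for loss in 2.4. Section 3.4 describes a case-by-case evaluation and not automatic withdrawal.

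Much of this stands. Loss of outcomes is a likely consequence and not a stated one, and no size can be shown. But the point rests on a rule that the article does state. The passages that favour follow-up say what is wanted; they do not tell a site that a patient withdrawn under 2.9 must still be assessed. The 10% allowance protects the number of patients, not the comparison if losses differ by arm.

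Three stronger readings are tempting and should not be drawn.

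- A reader might infer that the list is almost wholly about treatment. It is not: items 4 and 6 also speak of being unable to continue.
- A reader might see a contradiction between item 6 and section 3.5, which says "If any serious adverse event occurs, the intervention will be stopped immediately". The two can be read in sequence: 3.5 stops the drug, and item 6 applies if the patient also cannot continue.
- A reader might infer that listing death in item 6 loses mortality data. A death is a known outcome; it only needs to be recorded as one.

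It is also fair to say that splitting the list will not produce a bedside score for someone already discharged or transferred. How such a missing score is analysed belongs in the analysis plan.

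**Conclusion.** The concern holds as a fault in a stated rule. Sections 2.9 and 3.4 allow a decision about the drug to become a withdrawal from the study, which conflicts with the intention-to-treat analysis in 3.7. The efficacy score is most at risk; 28-day and 1-year status of withdrawn survivors may also be affected. The size is unknown: 1.8 points of an arm's rate per lost outcome is a scale, not an estimate, and neither bias nor inadequate power has been shown. The conclusion assumes that sites follow the text as written and that no fuller protocol instructs them to keep these patients in follow-up. It should be corrected, because it is cheap to put right beforehand and cannot be repaired once data have gone uncollected.

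**What to change.** Split section 2.9 into two lists.

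1. **Stopping the study drug:** drug-related adverse event, another serious disease, poor compliance, intolerance, giving up treatment, serious adverse event.
2. **Withdrawal from the study:** only when the patient or family withdraws consent to follow-up. The second half of item 3 belongs here.

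Then state that:

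- patients under list 1, and those discharged or transferred, stay in follow-up and in the intention-to-treat analysis;
- the day-14 syndrome score is taken while the patient is in hospital, and after discharge or transfer vital status and readmission are collected by the telephone follow-up already planned;
- death is recorded as an outcome and not as a withdrawal.

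Reword section 3.4 so that the evaluation asks whether the drug can continue.

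The cost is wording in 2.9 and 3.4 and one case report form field for the date and reason of the drug stop. The downside is the work of following patients who stopped the drug, on the existing schedule. No patients or visits are added.

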### Test drugs

2.10

Test drugs are JWQYD decoction and JWQYD mimetic agent (placebo). The placebo will be provided by Sichuan Green Pharmaceutical Technology Development Co., Ltd. (Sichuan, China). The ingredients of JWQYD are 30 g of prepared aconite, 15 g of Amomum, 30 g of tortoise shell, 10 g of ephedra, 10 g of dried ginger, and 12 g of licorice. All the ingredients are purchased and brewed by the pharmacy department of the Affiliated Hospital of Chengdu University of TCM. The above drugs will be administered at a dose of 25 ml intranasally or orally 4 times a day (to a total of 100 mL per day). The placebo is composed of starch without any active ingredients. The color and taste of the placebo are the same as that of the TCM.

## Intervention

3

### Treatment plan

3.1

Both groups will be treated with Western medicine in accordance with the “Diagnosis and Treatment Guidelines for Acute Lung Injury/Acute Respiratory Distress Syndrome” formulated by the severe medicine branch of the Chinese Medical Association in 2006,^[24]^ which includes active treatment of the primary disease, respiratory support (invasive mechanical ventilation), fluid management, prostaglandin E, sedation and analgesia, and nutritional support.

Western medicine combined with JWQYD: In addition to Western medical treatment, we will administer the decoction of qianyang dan, 25 mL intranasally or orally 4 times a day.

**Western medicine:** Patients in the western medicine treatment group will receive 25 ml of the placebo intranasally or orally, 4 times a day. Index observation should be consistent with the treatment group of integrated traditional Chinese and Western medicine.

### Determination of results

3.2

Since a holistic view of the patient is the core value of TCM, there is no single index that can predict their rehabilitation in order to evaluate the efficacy of JWQYD. Therefore, ARDS needs to be comprehensively evaluated.

1. Efficacy rate: The efficacy rate will be calculated according to the TCM syndrome score (Table 3).^[23]^ The total efficacy rate (%) = (clinical control + significant effect + effective)cases/(total cases × 100%). The score reduction (%) = (points before treatment - points after treatment)/(points before treatment × 100%). The TCM syndrome score will refer to the standard for the diagnosis and curative effect of TCM syndrome issued by the Chinese Society of TCM in 2012.

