### Sample size

2.4

Calculating the sample size was based on the effective rate. According to previous research, the effective rate for the treatment group with integrated traditional Chinese and Western medicine is 65.2%, and effective rate for the group with Western medicine alone is 34.8%. The software Power Analysis and Sample Size version 11.0 (PASS 11.0)was used to calculate the sample size of the 2 groups, assuming that 10% of patients are likely to be lost during follow-up, a total of 110 patients will be enrolled.

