**Table 3 T3:**
[figure not shown]
Quantitative standard for the classification of symptoms and signs.

The criteria for determining the therapeutic effect of TCM will be formulated in accordance with the guiding principles for clinical research for new TCM drugs^[25]^ (Trial) and the criteria for the therapeutic effect of the diagnosis of diseases and syndromes of TCM issued by the Chinese Society of TCM.

(1)Cure: the clinical symptoms and signs disappear or basically disappear, and the laboratory examination reveals visible improvement. The TCM syndrome score is reduced by more than 95%.(2)Significant effect: the clinical symptoms, signs, and laboratory tests are significantly improved. The TCM syndrome score is reduced by ≥70%.(3)Effective: the clinical symptoms, signs, and laboratory tests are improved. The TCM symptom score is reduced by ≥30%.(4)Invalid: the clinical symptoms and signs are not improved or have worsened. There is a < 30% reduction in the TCM symptom score.

2. PɑO2/FiO2: before and after the intervention, we will perform arterial blood gas analyses to measure changes in the PɑO2/FiO2.

3. Extravascular pulmonary water index: will be obtained from the PiCCO monitor (It is a tool to detect the main hemodynamic parameters of severe patients)

4. Length of time with ventilator: the time with the ventilator will be 14 days from the patient participating in the trial to the treatment.

5. ICU length of stay: the actual length of stay = date of leaving the ICU - date of entering the ICU + 1.

6. 28-day mortality: the mortality rate from the beginning of the trial to the 28th day will be recorded.

7. Follow-up records: During the follow-up period, the all-cause mortality, respiratory failure mortality, and readmission rate in the 1-year period after discharge will be recorded. Criteria for readmission: subjects readmitted for ARDS or other respiratory diseases, not including any other disease or reason. If readmission occurs during the follow-up period, the readmission rate will not be recorded during the follow-up period. Readmission rate = number of patients readmitted/number of patients who completed follow-up.

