## Discussion

4

ARDS is a major public health concern that seriously affects the quality of life and endangers the life of patients. At present, there is no specific treatment for ARDS; management primarily relies on supportive care. The economic burden of ARDS is a pressing concern worldwide.^[26,27]^ Therefore, finding effective treatment methods to improve prospects is urgent. At present, a large sample study to determine the efficacy and safety of JWQYD for the treatment of ARDS is lacking, so we will conduct a prospective randomized controlled trial to determine the risks and benefits of JWQYD in the treatment of ARDS.

This study has the following advantages: from the perspective of evidence-based medicine, this study is designed as a randomized, double-blind, placebo-controlled trial, which is considered the most authoritative research method. At the same time, this is a multicenter study conducted in 4 comprehensive Grade-A hospitals in China, which improves the external effectiveness and representativeness of the sample and reduces the risk of selection bias. Additionally, to ensure quality, all staff in the study will be required to complete a SOP (Standard Operation Procedure) training of the study procedure beforehand. Since the main stage of the study will be carried out during hospitalization, the staff will be able to quickly identify and manage adverse reactions to ensure the safety of the subjects. After discharge, researchers will maintain good telephone communication with patients and their families. However, there are some limitations to the design of the study, such as the failure to ensure that a 14-day treatment period will be the ideal length.

In summary, the purpose of this study is to determine whether JWQYD can be used as an adjuvant therapy with Western medicine in the treatment of ARDS patients, and to potentially provide objective evidence of its effectiveness and safety. If the hypothesis is confirmed, that is to say, the comprehensive plan of integrated traditional Chinese and Western medicine is relatively safe and more effective than treatment with Western medicine alone, then it can be recommended that patients with ARDS be treated with the qianyang pill to improve their clinical course.

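### The outcome that decides efficacy is left open: the trial is sized on the effective rate, but section 3.2 disclaims any single index and ranks none of nine outcomes

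*Protocol article*

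**What the plan says.** Four places in the protocol article bear on this.

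- **Section 2.4 (Sample size):** "Calculating the sample size was based on the effective rate", with 65.2% against 34.8%, 10% loss and 110 patients in total. No other outcome enters the calculation.
- **Section 3.2 (Determination of results):** the opening says "there is no single index that can predict their rehabilitation in order to evaluate the efficacy of JWQYD", and continues "Therefore, ARDS needs to be comprehensively evaluated". Seven numbered items follow. The first is the efficacy rate ("The efficacy rate will be calculated according to the TCM syndrome score"). The others are PaO2/FiO2, extravascular lung water index, ventilator time, ICU stay, 28-day mortality, and a follow-up item holding three 1-year outcomes: all-cause mortality, respiratory-failure mortality and readmission. That makes nine outcomes. None is called primary or secondary, and no rule says how they combine into a judgement.
- **Section 3.7 (Statistical analyses):** one general threshold, "The difference will be statistically significant when *P* ≤ .05", attached to no particular outcome.
- **Section 4 (Discussion):** if the combined regimen proves relatively safe and "more effective than treatment with Western medicine alone, then it can be recommended that patients with ARDS be treated" with the study preparation. The outcome on which this is judged is not named.

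**The concern.** Sections 2.4 and 3.2 pull in opposite directions. The first treats the effective rate as the quantity the trial exists to detect. The second says that no one measure can carry the judgement of efficacy, and puts a comprehensive evaluation without a stated rule in its place. Section 4 then draws a practical consequence from a finding of superiority that could be met in several ways.

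If a favourable result on lung water, ICU stay or the syndrome score could each be presented as confirming the hypothesis, the error rate of the trial's conclusion is no longer the 5% of a single test, and the outcome for which the trial has power has no declared standing. Section 1 cites mortality of 30% to 40% in ARDS, so it matters whether the conclusion rests on a pre-declared outcome or on whichever one turned out well.

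**Working it through.** **1. Reproducing the sample size, to see what the design is built on.** Inputs from section 2.4: p1 = 0.652, p2 = 0.348, 10% loss. Power and sidedness are not stated; 80% and two-sided 0.05 are assumed here. With d = 0.304 and mean proportion 0.5, the pooled formula is

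n = [1.96·√(2·0.5·0.5) + 0.842·√(0.652·0.348 + 0.348·0.652)]² / 0.304² = 41.3 per arm.

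With continuity correction: (41.3/4)·[1 + √(1 + 4/(41.3·0.304))]² = 47.6, so 48 per arm. Allowing for loss, 48/0.9 = 53.3, so 54 per arm and 108 in total, within 2 of the stated 110. The figure is consistent with one test of one outcome at 0.05.

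**2. Counting outcomes.** Six single-outcome items plus three outcomes in item 7 give nine. Five are rates (efficacy, 28-day mortality and the three 1-year outcomes). Section 3.7 names a t-test or a nonparametric test for measured data and no test for rates.

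**3. Error rate if any one outcome may carry the claim.** This is an assumption about use, not a stated rule.

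- Independent outcomes, either direction: 1 − 0.95⁹ = 0.370.
- Independent outcomes, favouring JWQYD only: 1 − 0.975⁹ = 0.204, against 0.025 for one outcome.
- Correlated outcomes: Zᵢ = √ρ·U + √(1−ρ)·eᵢ, all standard normal. The chance of at least one |Zᵢ| > 1.96 is 1 − ∫ φ(u)·[Φ((1.96 − √ρ·u)/√(1−ρ)) − Φ((−1.96 − √ρ·u)/√(1−ρ))]⁹ du. For the favourable direction, the second Φ term is dropped.

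| Common correlation | At least one P ≤ .05 | At least one in favour of JWQYD |
|---|---|---|
| 0 | 37.0% | 20.4% |
| 0.3 | 32.6% | 16.5% |
| 0.5 | 26.9% | 13.5% |
| 0.7 | 20.2% | 10.1% |
| 0.9 | 12.4% | 6.2% |
| One outcome decides | 5% | 2.5% |

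With one outcome per numbered item (seven), the two-sided figures are 30.2% if independent, 23.0% at correlation 0.5 and 17.8% at 0.7.

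**4. What each way of closing the gap costs.** With 55 per arm and 10% loss, 55·0.9 = 49.5, so 49 are evaluable per arm.

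- Effective rate as sole primary at 0.05: power about 86% by the pooled test, and about 80% (81%) with continuity correction.
- Nine co-equal outcomes with Bonferroni, 0.05/9 = 0.0056: pooled power on the effective rate falls to about 60%. Reaching 80% would need 70 evaluable per arm; 70/0.9 = 77.8, so 78 per arm and 156 in total.

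**The case against.** The strongest reply is that the effective rate is already the primary outcome in all but name: it is listed first and the trial is sized on it. On that reading the remark about no single index merely explains why several measures are collected, and the error rate is 5%. The article's abstract and its schedule figure are not shown here and may carry a primary label. A multiplicity method for secondary outcomes may properly sit in an analysis plan that is not shown, so its absence is no fault.

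Much of this stands. A reader might infer that the trial will test nine outcomes at 0.05 and claim success on any one, so that its false-positive rate is several times nominal. The document does not support this as fact. It gives a general threshold, names no test for the five rates, and says only that the mortality and follow-up outcomes will be recorded. A comprehensive evaluation could also be a joint requirement. If all nine had to reach P ≤ .05 in the same direction, the false-claim rate would be about 0.02% at correlation 0.5 and 0.2% at 0.7. The 37% figure is an upper one: respiratory-failure deaths are a subset of all deaths, ventilator time and ICU stay overlap, and exact tests on few events are conservative.

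What the reply does not remove is the conflict in the text. Section 3.2 speaks of evaluating the efficacy of JWQYD, not just of describing recovery, and disclaims a single index for that purpose. Section 2.4 relies on one. Section 4 does not say which reading governs. A label elsewhere would still have to be reconciled with section 3.2.

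**Conclusion.** The concern holds as an unresolved conflict about which outcome decides efficacy, not as a demonstrated inflation of error. Depending on the reading, the chance of a nominally significant result under no effect runs from 5% (effective rate alone) to between 12% and 37% (any of nine outcomes, correlation 0.9 down to 0). In favour of JWQYD, the range is 2.5% against 6% to 20%. These figures assume two-sided tests of exact 5% size, no true effect on any outcome and a common correlation. The lower end is more plausible for the overlapping outcomes. The conclusion rests on what sections 2.4, 3.2 and 4 say, and does not depend on a missing adjustment method. It should be settled before unblinding, since a primary outcome chosen after results are seen gives no protection.

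**What to change.** Reconcile sections 2.4, 3.2 and 4:

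- In 3.2, declare the efficacy rate at the end of the 2-week treatment as the single primary outcome, tested two-sided at 0.05. The time point is inferred from the treatment period, because 3.2 refers only to the score after treatment; the sponsor should confirm it. Reword the opening so that several measures describe recovery while one decides efficacy.
- Label all other outcomes secondary, reported as estimates with 95% confidence intervals and no confirmatory claim.
- In section 4, tie the conclusion on efficacy to the primary outcome.

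This is a change of wording. The sample size of 110 and the power on the effective rate are unaffected. The price is that a lone significant secondary outcome can no longer support the efficacy claim.
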